### Sample size calculation

The primary outcome of this non-inferiority trial is the mean VAS score in the first postoperative 24 h in TMQLB group 1 (ropavacaine 0.4 ml/kg body weight) and the TPVB group. Hence, we used the sample size estimation with the non-inferiority test for the difference between two means using PASS 15 software. A higher VAS score in clinical practice indicates that the patients suffer worse pain. No non-parametric adjustment was used in the sample size calculation. We used statistical power of 90% and two-sided α of 0.05. Based on our pilot study, the VAS scores in TMQLB group 1 and the TPVB group were 3.35 and 3.08, respectively, and the standard deviation (SD) of the mean VAS score was 0.5. The non-inferiority margin was set as 0.616 (20% of the VAS score in the TPVB group). The target sample size for each group is at least 36 participants. Considering a potential dropout rate of 10% in the postoperative data collection, we plan to include 40 patients in each group.

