### Data analysis

We will first describe the baseline characteristics of the participants and compare the group difference using the standardized difference; a standardized difference smaller than 0.2 will be considered acceptable deviation between groups [19]. The distribution of the variables will be checked by visual inspection of the histogram. Normally and non-normally distributed variables will be described by the mean ± SD or median (interquartile range (IQR)).

In all data analyses, we will first compare TMQLB group 1 with the TPVB group. If the result is negative, then we will compare data for TMQLB group 2 with the TPVB group to explore whether increasing the amount of local anesthetic would improve the outcome of TMQLB.

Since the primary outcome of the mean VAS score in the first postoperative 24 h is generally normally distributed as reported by Dai et al. [13], the result will be expressed as mean ± SD. Student’s *t* test will be used to compare the difference in the mean postoperative VAS score between TMQLB group 1 and the TPVB group, and the mean difference with corresponding one-sided 95% CI will be calculated. If the upper bound of the one-sided 95% CI is smaller than 0.616, we will reject the null hypothesis in the non-inferiority test and conclude that the mean VAS score in the first postoperative 24 h in TMQLB group 1 is non-inferior to that in the TPVB group.

For the secondary outcomes, the mean difference in the VAS score between TMQLB group 2 and TPVB group, cumulative morphine consumption and long-term VAS scores will be analyzed using the non-inferiority test, while other variables will be analyzed using the superiority test. For continuous data, Student’s *t* test will be used for parametric data analysis and the Mann-Whitney test will be used for non-parametric data analysis, including data on morphine consumption which are often reported as highly skewed. The time-to-event data including time of bowel movement recovery, ambulation time and length of hospital stay will be analyzed by Kaplan-Meier estimates to obtain the survival curves and then the log-rank test will be used to compare curves between groups.

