## Discussion

Although QLB is gaining popularity as analgesia in abdominal surgery, there has been limited clinical study of its clinical efficacy compared with other truncal block techniques. Most of the current studies concentrate on the comparison of QLB with other abdominal blocks, especially the transversus abdominis plane (TAP) block, because QLB was originally proposed as a different form of TAP [4, 5, 15, 16]. Also, the analgesic mechanism of TMQLB is still controversial. The anatomical work performed by Børglum et al. [9] reveals that in TMQLB the injectate spreads cephalad to the thoracic paravertebral space. This convincing study prompted us to speculate that TMQLB may have a similar analgesic profile to TPVB, which is essentially a thoracic truncal block, and this inspired us to conduct a trial to compare these two block techniques and further validate the theory from a clinical aspect.

The expected results will provide clinical evidence to verify the analgesic mechanism of TMQLB put forward by Børglum and promote its application in intraperitoneal and retroperitoneal surgery. Furthermore, if the efficiency of TMQLB is equal to that of TPVB, TMQLB could replace TPVB in abdominal surgery because it is relatively safe and convenient to perform, while TPVB implicates a possibility of pneumothorax, dural puncture and hematoma in the thoracic paravertebral space [10, 14].

As the mechanism of the injectate of TMQLB reaching the paravertebral space is primarily by spreading via the pathway posterior to the arcuate ligaments, it could be assumed that the amount of the injectate will consequently determine the extent to which the thoracic nerves are blocked. Henceforth, we designed three intervention groups with two dosing groups for TMQLB to explore whether the amount of injectate would improve the coverage and analgesic effect. This may also provide a clue to the appropriate dosage for anesthetics in TMQLB.

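### The stated two-sided α of 0.05 contradicts both the sample size of 36 per group and the one-sided 95% bound, which describe a one-sided 5% test

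*Protocol article*

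**What the plan says.** Three statements in the protocol article fix the primary test of TMQLB group 1 against TPVB.

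- **Error rate and power** (Sample size calculation): "We used statistical power of 90% and two-sided α of 0.05".
- **Sample size** (same section): "The target sample size for each group is at least 36 participants", raised to 40 for 10% dropout. The method is given as follows: "we used the sample size estimation with the non-inferiority test for the difference between two means using PASS 15 software".
- **Decision rule** (Data analysis): "If the upper bound of the one-sided 95% CI is smaller than 0.616, we will reject the null hypothesis in the non-inferiority test".

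The planning values are that "the VAS scores in TMQLB group 1 and the TPVB group were 3.35 and 3.08, respectively" and that "the standard deviation (SD) of the mean VAS score was 0.5". The margin is 0.616, which is 20% of 3.08.

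**The concern.** A non-inferiority test looks at one side of the interval only. A two-sided α of 0.05 leaves 2.5% on that side and corresponds to a one-sided 97.5% bound, which is the upper limit of the two-sided 95% interval. A one-sided 95% bound leaves 5%. Both statements concern the same comparison, so both cannot hold.

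Two things depend on which one governs:

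- **The false non-inferiority rate.** A reader of the sample size section will take it to be 2.5%. Under the written decision rule it is 5%.
- **The power.** The stated 90% can belong to only one of the two tests at this sample size.

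If the question stays open until the data are in, a borderline result could be read either way.

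**Working it through.** **Inputs** (all from Sample size calculation)

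- Expected difference: 3.35 − 3.08 = 0.27, with TMQLB group 1 worse
- SD: 0.5
- Margin: 0.20 × 3.08 = 0.616
- Distance from the expected difference to the margin: 0.616 − 0.27 = 0.346
- Power: 90%, so z = 1.282

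**Step 1. Which α gives 36?** The normal-approximation formula per group is n = 2 (z₁₋α + z_power)² SD² / 0.346².

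- One-sided 0.05: 2 × (1.645 + 1.282)² × 0.25 / 0.1197 = 35.8, rounded up to **36**. Then 36 / 0.9 = 40. Both stated figures are reproduced.
- One-sided 0.025 (the stated two-sided 0.05): 2 × (1.960 + 1.282)² × 0.25 / 0.1197 = 43.9, rounded up to **44**. Then 44 / 0.9 = 48.9, so 49 per group. Neither stated figure is reproduced.

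The noncentral t distribution gives 37 and 45. The 36 therefore comes from the normal approximation at one-sided 0.05, and the gap of one patient between 36 and 37 is immaterial.

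Other routes to 36 at one-sided 0.025 fail. A true difference of 0 gives 14, and 80% power gives 33.

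**Step 2. Power under each reading** (noncentral t, normal approximation in brackets)

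| Evaluable per group | One-sided 0.05 | One-sided 0.025 |
|---|---|---|
| 36 | 89.7% (90.2%) | 82.5% (83.5%) |
| 40 | 92.3% (92.6%) | 86.4% (87.2%) |

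**Step 3. Where the verdict changes.** With 36 per group and an observed SD of 0.5, the standard error is 0.5 × √(2/36) = 0.1179. On 70 degrees of freedom, the largest observed difference that still passes is:

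- one-sided 95% bound: 0.616 − 1.667 × 0.1179 = 0.420
- one-sided 97.5% bound: 0.616 − 1.994 × 0.1179 = 0.381

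An observed difference between about 0.38 and 0.42 is non-inferior under the written rule and not under the stated α. Under the planning assumptions, about 89.7% − 82.5% = 7.2% of trials would end in that zone.

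**The case against.** The strongest reply is that two of the three statements agree. The sample size and the decision rule both fit one-sided 0.05, and the rule is written out in full with its bound and margin. The likeliest explanation is one wrong word in the sample size section. On that reading the trial has about 90% power for the test it will run. This stands, and it limits the point in three ways.

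- **Underpowering.** A reader might infer that the trial is simply underpowered at 83%. The documents do not support that. The figure holds only if the stated α governs.
- **The 5% rule itself.** A reader might infer that a one-sided 5% rule is an error. It is a possible choice, but the sample size section then has to say so.
- **A non-inferior result that is also statistically worse.** A reader might infer that the mismatch lets the trial declare success while TMQLB is shown to be worse. That outcome is plausible, but the mismatch does not cause it. With 36 per group and a true difference of 0.27, its probability is about 51% under the written rule and still about 44% under the stricter one. It arises because the plan assumes a deficit lying inside the margin.

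The Discussion does contain the phrase "if the efficiency of TMQLB is equal to that of TPVB, TMQLB could replace TPVB in abdominal surgery". This is a conditional remark. The planned conclusion in Data analysis, like the hypothesis in Objectives, is non-inferiority.

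The reply does not remove the contradiction. It concerns the error rate of the primary test, and only the sponsor can say which statement was intended.

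**Conclusion.** The point holds as an internal contradiction about the primary test. The sample size section allows 2.5% in the non-inferiority direction, while the sample size and the decision rule both correspond to 5%.

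- **If the stated α governs:** 90% power needs 44 to 45 evaluable per group, and the trial has about 83% with 36 or 86% with 40.
- **If the decision rule governs:** power is about 90% with 36 evaluable and 92% with 40, and the α label is wrong. The arithmetic favours this reading but cannot prove it.

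These figures rest on the protocol's planning values and on equal groups analysed by an unadjusted t test. The band of 0.38 to 0.42 also assumes an observed SD of 0.5 and 36 evaluable patients per group.

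**What to change.** Make α, sample size, power and bound agree, and record the choice before results are seen. At submission, recruitment was still under way (Trial status). Two routes are open:

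1. **Keep the two-sided α of 0.05.** Declare non-inferiority only if the upper limit of the two-sided 95% interval (a one-sided 97.5% bound) is below 0.616. Keep 40 per group and restate power as about 83% (36 evaluable) to 86% (40 evaluable). The cost is a less favourable power statement and a slightly stricter criterion. Holding 90% power as well would take 49 to 50 randomised per group (44 / 0.9 and 45 / 0.9).
2. **Keep the one-sided 95% rule.** Correct the sample size section to a one-sided α of 0.05. The 36, the 40 and the 90% then stand, and the 5% false non-inferiority rate is openly stated.

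Under either route, also report the two-sided 95% interval for the difference. The plan itself expects TMQLB group 1 to be worse by 0.27, and readers should see both limits. Both routes change wording only and need no extra patients.

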### Data analysis

We will first describe the baseline characteristics of the participants and compare the group difference using the standardized difference; a standardized difference smaller than 0.2 will be considered acceptable deviation between groups [19]. The distribution of the variables will be checked by visual inspection of the histogram. Normally and non-normally distributed variables will be described by the mean ± SD or median (interquartile range (IQR)).

In all data analyses, we will first compare TMQLB group 1 with the TPVB group. If the result is negative, then we will compare data for TMQLB group 2 with the TPVB group to explore whether increasing the amount of local anesthetic would improve the outcome of TMQLB.

Since the primary outcome of the mean VAS score in the first postoperative 24 h is generally normally distributed as reported by Dai et al. [13], the result will be expressed as mean ± SD. Student’s *t* test will be used to compare the difference in the mean postoperative VAS score between TMQLB group 1 and the TPVB group, and the mean difference with corresponding one-sided 95% CI will be calculated. If the upper bound of the one-sided 95% CI is smaller than 0.616, we will reject the null hypothesis in the non-inferiority test and conclude that the mean VAS score in the first postoperative 24 h in TMQLB group 1 is non-inferior to that in the TPVB group.

For the secondary outcomes, the mean difference in the VAS score between TMQLB group 2 and TPVB group, cumulative morphine consumption and long-term VAS scores will be analyzed using the non-inferiority test, while other variables will be analyzed using the superiority test. For continuous data, Student’s *t* test will be used for parametric data analysis and the Mann-Whitney test will be used for non-parametric data analysis, including data on morphine consumption which are often reported as highly skewed. The time-to-event data including time of bowel movement recovery, ambulation time and length of hospital stay will be analyzed by Kaplan-Meier estimates to obtain the survival curves and then the log-rank test will be used to compare curves between groups.

In the case of data missing or dropouts, data analysis will be performed according to the intention-to-treat principle. The results of this trial will be reported according to the Consolidated Standards of Reporting Trials (CONSORT) statement [17]. All data analysis will be performed using SPSS software (version 22; SPSS Inc., Chicago, IL, USA).

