**Methods:**

This trial is a prospective, randomized, single-center, open-label, parallel, three-arm, non-inferiority trial. We intend to include 120 participants undergoing laparoscopic nephrectomy and before surgery they will be randomized into three groups for postoperative pain control: TMQLB experimental group 1 (0.4 ml/kg body weight 0.5% ropivacaine), TMQLB experimental group 2 (0.6 ml/kg body weight 0.5% ropivacaine) or TPVB control group (0.4 ml/kg body weight 0.5% ropivacaine at vertebra T10). Patients will be excluded if they have allergy to anesthetics, infection at the injection site, are on coagulopathy or anticoagulants, on analgesics for chronic illness, have history of substance abuse or have a barrier to communication. Morphine is given in boluses of 1.5~2 mg by intravenous patient-controlled analgesia (IPCA) in the first 48 h after surgery. The primary outcome is the difference between TMQLB group 1 and the TPVB group in the mean visual analogue scale (VAS) pain score in the first 24 h after surgery. Secondary outcomes are the difference between TMQLB group 2 and the TPVB group in the mean VAS score in the first 24 h after surgery, cumulative morphine consumption, long-term pain control, dermatomal distribution of sensory loss, nausea score, pruritus score, ambulation time, time till recovery of bowel movement, quality of recovery, postoperative length of hospital stay and patient satisfaction with anesthesia. Safety data on procedure-related complications will also be summarized.

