#### Secondary outcomes

Secondary outcomes are as follows:Mean VAS score in the first postoperative 24 h between TMQLB group 2 and the TPVB group. In theory, the dose of local anesthetic in TMQLB group 1 is lower than that in TMQLB group 2, hence, if group 1 satisfies the non-inferiority hypothesis, the mean VAS score in group 2 should also be non-inferior to that in the TPVB group. If not, the results of the comparison between TMQLB group 2 and the control will be hypothesis-generating.Cumulative morphine consumption, which will be registered at 0, 2, 4, 8, 12, 24, 48 and at 72 h and 7 days after surgery, and will be calculated as the sum of the values.Long-term pain control, which will be evaluated by VAS at 48 and 72 h and at 7 days after surgery.Dermatomal distribution of sensory loss, which will be evaluated at 10, 20, 30 and 40 min after the intervention by pinprick test using Von Frey filaments.Nausea score, which will be recorded at 0, 2, 4, 8, 12, 24 and 48 h after surgery.Pruritus score, which will be recorded at 0, 2, 4, 8, 12, 24 and 48 h after surgery.Ambulation timeTime of recovery of bowel movement (defined as the time to first flatus).Quality of recovery evaluated by the self-assessment quality of recovery (QoR) scale at 3 days and 5 days after surgery. The QoR is a 15-item questionnaire, scored on a scale of 0–10 pertaining to the patient’s comfort, support system, pain, wellbeing and ability to carry out daily activities, where 0 indicates none of the time and 10 indicates all of the time [11].Length of postoperative of hospital stay.Patient satisfaction with anesthesia evaluated using the Chinese version of the Bauer questionnaire at 48 h after surgery [12].

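### The plan contradicts itself on when TMQLB group 2 is compared with TPVB, conditions that comparison on group 1 failing, and names no group 2 versus group 1 contrast for the volume question

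*Protocol article*

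**What the plan says.** The second paragraph of Data analysis sets the order: "In all data analyses, we will first compare TMQLB group 1 with the TPVB group". It continues: "If the result is negative, then we will compare data for TMQLB group 2 with the TPVB group". The stated purpose of that second step is to explore whether more local anesthetic improves the result. Nothing is said there about group 2 when group 1 succeeds.

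Three other places carry no such condition:
- Abstract, Methods: "Secondary outcomes are the difference between TMQLB group 2 and the TPVB group in the mean VAS score in the first 24 h after surgery".
- The list under Secondary outcomes: the same comparison is its first item.
- Data analysis, paragraph on secondary outcomes: the VAS comparison of group 2 against TPVB is assigned the non-inferiority test, as are morphine consumption and the later VAS scores.

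Secondary outcomes also makes the standing of the group 2 result depend on group 1. It reasons from theory that "if group 1 satisfies the non-inferiority hypothesis, the mean VAS score in group 2 should also be non-inferior to that in the TPVB group". It then adds: "If not, the results of the comparison between TMQLB group 2 and the control will be hypothesis-generating".

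The Discussion gives the reason for having two TMQLB arms: "to explore whether the amount of injectate would improve the coverage and analgesic effect". No section names a comparison of group 2 with group 1. The log-rank test is described as between groups, without saying which pairs.

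**The concern.** A reader cannot tell from the article whether group 2 will be compared with TPVB if group 1 succeeds. One paragraph implies not; three other places imply that it will be.

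The conditional rule is also the reverse of what protects the error rate. A fixed sequence opens the next hypothesis after a success, at no cost in α. Opening it after a failure gives a second chance at a positive result, and leaves the arm uncompared where a confirmatory claim could have been made. In the success branch the text offers an expectation from theory, although whether a larger volume does at least as well is part of what the third arm was added to learn.

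Finally, whether volume matters is a question about group 2 against group 1. If group 1 fails and group 2 then passes against the same control, this can easily be read as a volume effect when chance alone produced it.

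**Working it through.** **Inputs.** From Sample size calculation: expected means 3.35 (group 1) and 3.08 (TPVB), so a difference of 0.27; SD 0.5; margin 0.616; 36 evaluable and 40 enrolled per group; power 90%. From Data analysis: group 1 passes if the upper bound of a one-sided 95% CI is below 0.616. No expected mean is given for group 2, so its true difference is assumed below.

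**Reproducing the plan's figure.** n = 2 × SD² × (z₀.₉₅ + z₀.₉₀)² / (margin − difference)² = 2 × 0.25 × (1.645 + 1.282)² / 0.346² = 35.8, so 36 per group. Then 36 / 0.9 = 40. This matches at one-sided 0.05. The sample size section states a two-sided α of 0.05; that mismatch is a separate matter, and the one-sided 95% decision rule is used here.

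**How often group 1 succeeds.** SE = 0.5 × √(2/36) = 0.1179. P(pass) = Φ(0.346/0.1179 − 1.645) = Φ(1.29) ≈ 0.90. Followed literally, the conditional rule leaves group 2 uncompared on mean VAS in about 90% of trials under the planning assumptions.

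**Expectation versus test in that branch.** The two comparisons share the TPVB arm, so their estimates have correlation 0.5. Simulation (400,000 runs, 36 per arm) gives P(group 1 passes and group 2 would fail its own test):
- about 7% if group 2's true difference is also 0.27;
- about 85% if group 2 is truly at the margin.

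**Fail-then-pass with no volume effect.** With identical true differences in both TMQLB arms, P(group 1 fails, group 2 passes):
- at 0.27: 6.6% (simulation);
- maximum: this occurs where each arm passes half the time, at 0.616 − 1.645 × 0.1179 = 0.422. There P(both pass) = 1/4 + arcsin(0.5)/(2π) = 1/3, so one-way discordance is 1/2 − 1/3 = 1/6, or 16.7%.

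**Second chance.** With both arms truly at the margin, P(at least one passes) is 8.8%, against 5% for one test.

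**The missing contrast.** For group 2 minus group 1 on mean VAS, the 95% CI half-width is 1.96 × 0.1179 = 0.23 at 36 per group. Two-sided 5% power is 62% (n = 36) to 67% (n = 40) for a true difference of 0.27, and 20% to 22% for 0.135.

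**Cost of always comparing group 2 with TPVB.** No patients are added. At one-sided 0.05, power with 36/40 per group is 90%/93% if group 2's true difference is 0.27, and 58%/61% if it is 0.40.

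**The case against.** The strongest reply is that the article, read as a whole, does not leave group 2 untested. Mean VAS for group 2 is a listed secondary outcome with an assigned test, and Secondary outcomes already calls the result hypothesis-generating if group 1 fails. Read together, these come close to a proper fixed sequence. That reply stands in part, and is why the point is a contradiction to resolve. It does not dispose of the paragraph that conditions group 2 on a negative result in all analyses, which for outcomes other than mean VAS is the only stated rule on when group 2 is compared.

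Several stronger readings are tempting, and the documents do not support them:
- *Group 2 is analysed only if group 1 fails and is otherwise declared non-inferior without data.* The unconditional listing and test say otherwise. The theoretical sentence is an expectation; nowhere does the article say that a conclusion will be drawn from it alone.
- *The error rate for group 2 is 8.8%.* That counts a pass after failure as a claim, which the hypothesis-generating label largely disclaims for mean VAS. The label is not extended to the other outcomes.
- *The group 2 estimate is biased towards success after group 1 fails.* At a true difference of 0.27 the shared control shifts it by about +0.10 VAS points, which makes group 2 look worse.
- *The third arm contributes nothing if group 1 succeeds.* Safety, complications and dermatomal spread are collected in every patient.

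The volume aim is also worded as exploratory, and a direct contrast at this sample size would be imprecise. Both are true, but an exploratory volume question still needs the contrast that addresses it.

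**Conclusion.** The point holds as an inconsistency together with a condition that runs the wrong way. The article gives incompatible rules for when group 2 is compared with TPVB. On the conditional rule, group 2 goes uncompared on mean VAS in about 90% of trials under the planning assumptions (difference 0.27, SD 0.5, 36 per group, one-sided 5%).

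The only stated route to the volume question can suggest an effect where none exists: in about 7% of trials at a common true difference of 0.27, and in at most about 17%. These figures assume normal estimates, equal SDs and a shared control. The group 2 effects are assumptions, because the article gives none.

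The primary comparison of group 1 with TPVB, its margin and its sample size are untouched. This should be fixed because it determines what the trial can conclude about group 2 and about volume, but it does not threaten the main result.

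**What to change.** Replace the conditional sentence in Data analysis with text to this effect:

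- *TMQLB group 2 is compared with TPVB, with an estimate and CI, for every outcome whatever the group 1 result.*
- *For mean VAS over 0–24 h, group 2 is formally tested for non-inferiority at the same α only if group 1 has been found non-inferior; otherwise the comparison is exploratory.*
- *After a negative group 1 result on any other outcome, the group 2 comparison on that outcome is likewise exploratory.*
- *The group 2 minus group 1 difference with its 95% CI is reported as an exploratory estimate for VAS, morphine consumption and dermatomal spread.*

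In Secondary outcomes, delete the inference that group 2 should be non-inferior because group 1 is, and keep the hypothesis-generating label. Describe the direct contrast as informing the volume question, not settling it, given its power of 62% to 67% for a true difference of 0.27.

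The cost is a change of wording and one additional contrast on data already being collected. No patients are added, and the fixed sequence needs no α adjustment. Recruitment was ongoing when the article was submitted; the change should be recorded before allocation is revealed, so that it cannot appear to follow the results.

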#### Postoperative analgesia

Each participant will receive standard postoperative intravenous patient-controlled analgesia (IPCA) at the end of surgery. Morphine is given in boluses of 1.5–2 mg as needed without baseline infusion in the first 48 h postoperatively, with a lockout time of 10 min. The 1-h limit is 6–8 mg morphine.

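### Morphine use and later VAS are labelled non-inferiority outcomes without a usable margin, and the Mann-Whitney test named for morphine tests only for no difference, so a moderate morphine excess cannot be ruled out

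*Protocol article*

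**What the plan says.** Under Data analysis the protocol article sorts the secondary outcomes by type of hypothesis. The group 2 VAS comparison comes under non-inferiority, and so do two further outcomes: "cumulative morphine consumption and long-term VAS scores will be analyzed using the non-inferiority test, while other variables will be analyzed using the superiority test". The next sentence chooses tests by data type and states that "the Mann-Whitney test will be used for non-parametric data analysis, including data on morphine consumption which are often reported as highly skewed". No shift, margin or confidence bound accompanies that test.

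The article states one margin and one decision rule:

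- Sample size calculation: "The non-inferiority margin was set as 0.616 (20% of the VAS score in the TPVB group", where the pilot TPVB mean was 3.08.
- Data analysis, for the primary comparison of TMQLB group 1 with TPVB: "If the upper bound of the one-sided 95% CI is smaller than 0.616, we will reject the null hypothesis in the non-inferiority test".

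The outcomes concerned are defined under Secondary outcomes. Morphine: "Cumulative morphine consumption, which will be registered at 0, 2, 4, 8, 12, 24, 48 and at 72 h and 7 days after surgery", then summed. Later pain: "Long-term pain control, which will be evaluated by VAS at 48 and 72 h and at 7 days after surgery".

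Under Postoperative analgesia, all arms receive patient-controlled morphine: "Morphine is given in boluses of 1.5–2 mg as needed without baseline infusion in the first 48 h postoperatively".

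**The concern.** A non-inferiority test needs a margin on the scale of the outcome and a rule that compares a bound with it. The article supplies both for the primary outcome. For morphine it supplies neither, and it names a procedure whose usual null hypothesis is equality. Two adjacent sentences therefore give the same variable a non-inferiority aim and a test of no difference. Failure to reject equality is not evidence that an excess is small.

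The conflict also affects the planned order of comparisons. In every analysis group 2 is to be compared with TPVB if the group 1 result is negative. For a morphine non-inferiority test without a margin, a negative result has no definition.

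Morphine matters more than most secondary outcomes here because it bears on how the primary result is read. Patients titrate it themselves throughout the 24 h in which the primary VAS is measured. A somewhat weaker block could yield a similar VAS at the price of more morphine. A reader who wants to interpret VAS non-inferiority as equal analgesia needs to know how large a morphine excess the data exclude.

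**Working it through.** **1. The plan's own figure.** Inputs from Sample size calculation: means 3.35 and 3.08 (difference 0.27), SD 0.5, margin 0.616, power 90%. With one-sided 0.05, which matches the one-sided 95% bound in Data analysis:

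n = 2 × 0.5² × (1.645 + 1.282)² / (0.616 − 0.27)² = 0.5 × 8.567 / 0.1197 ≈ 35.8, so 36 per group; 36 / 0.9 = 40.

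The stated 36 and 40 reproduce. They size the VAS comparison only; nothing in them concerns morphine.

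**2. Can 0.616 be borrowed?** 0.20 × 3.08 = 0.616, in VAS points. It cannot be applied to milligrams. For later VAS the unit fits but the derivation does not. As an illustration only, if the TPVB mean had halved to 1.54 by a later visit, 0.616 would be 0.616 / 1.54 = 40% of it instead of 20%.

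**3. What an ordinary Mann-Whitney test would show.** The article gives no morphine mean or SD, so the following are assumptions: log-normal consumption, CV 0.5 to 1.0 in both groups, and true TMQLB/TPVB ratios of 1.2, 1.5 and 2.0. The sample is 36 or 40 per group, with 4,000 simulated trials per setting and a two-sided 5% test. The last two columns give the power of a margin-shifted Mann-Whitney test (one-sided 0.05) when use is truly equal.

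| CV | n | p<0.05, ratio 1.2 | p<0.05, ratio 1.5 | p<0.05, ratio 2.0 | power, margin 1.2 | power, margin 1.5 |
|---|---|---|---|---|---|---|
| 0.5 | 36 | 0.349 | 0.943 | 1.000 | 0.476 | 0.968 |
| 0.5 | 40 | 0.390 | 0.960 | 1.000 | 0.514 | 0.980 |
| 0.8 | 36 | 0.180 | 0.657 | 0.978 | 0.278 | 0.765 |
| 0.8 | 40 | 0.187 | 0.700 | 0.990 | 0.297 | 0.799 |
| 1.0 | 36 | 0.137 | 0.505 | 0.922 | 0.233 | 0.642 |
| 1.0 | 40 | 0.161 | 0.557 | 0.950 | 0.238 | 0.686 |

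A true 20% excess is therefore non-significant in 1 − 0.390 = 61% to 1 − 0.137 = 86% of trials. A 50% excess is detected in about 51 to 96%, and a doubling in about 92 to 100%.

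**4. Check by hand.** The test is unchanged by taking logs, so the normal-shift formula applies on the log scale, with log-SD s = √ln(1 + CV²) and k = (ln r / s) × √(n/2) × √0.955.

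- CV 0.5, n = 40, r = 1.2: s = 0.472, k = (0.182 / 0.472) × 4.472 × 0.977 = 1.69; power Φ(1.69 − 1.96) = 0.39.
- CV 1.0, n = 36, r = 1.2: s = 0.833, k = 0.91; power Φ(0.91 − 1.96) + Φ(−0.91 − 1.96) = 0.15.

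Both agree with the simulation. For a ratio margin of 1.2 under equal use, Φ(k − 1.645) runs from Φ(0.91 − 1.645) = 0.23 to Φ(1.69 − 1.645) = 0.52.

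**5. Can a rank method show non-inferiority?** Yes, once a margin is built in. With the true ratio set at the margin (1.2 or 1.5), the shifted test wrongly declared non-inferiority in 4.6 to 5.8% of simulated trials, close to the nominal 5%.

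**The case against.** The strongest objection is that this is a journal article. Margins and interval methods for secondary outcomes are commonly left to a full protocol or SAP, and neither is shown. That tempers the missing-margin part: the margins may exist elsewhere. It does not remove the conflict, because the article itself gives morphine a non-inferiority aim and, in the next sentence, an unshifted test of difference.

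A second objection is that naming a test family need not mean an equality p-value. The article names Student's t test for the primary outcome and then applies it through a confidence bound against a margin. That is fair, and a reader should not infer that a Mann-Whitney analysis is incapable of showing non-inferiority; a shifted test or a Hodges-Lehmann bound can. But the article spells out the bound for the primary outcome and gives nothing equivalent for morphine.

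Three stronger readings are tempting and are not supported:

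- That nothing checks for a morphine difference. Morphine is recorded at nine times, including 24 h, and compared between groups, so a large excess would probably be seen.
- That the authors will report a non-significant result as non-inferiority. No sentence says so, and the primary rule suggests that they know the distinction.
- That the test would miss a 0.3 SD excess 76% of the time and a 0.5 SD excess 45% of the time. Those figures follow from a normal shift at 36 per group (k = 0.3 × √18 × √0.955 = 1.24; for 0.5, 2.07), whereas the article expects strong skew. For the same SD shifts on log-normal data with CV 0.5 to 1.0, the miss rates are about a third to two thirds and about 4 to 29%.

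**Conclusion.** The point holds as an internal conflict with a limited consequence. Morphine and later VAS carry a non-inferiority label, the only stated margin fits neither, and the test named for morphine is, as written, a test of no difference. The planned analysis would probably reveal a doubling of morphine use but could not rule out a moderate excess: at a true excess of 20%, p>0.05 would occur in roughly 61 to 86% of trials.

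These percentages rest on assumed log-normal data, CV 0.5 to 1.0, and 36 to 40 per group; none of the morphine inputs comes from the article. The conflict itself needs no assumption. It does not invalidate the primary VAS test, which has its own margin and rule; it limits how far a favourable VAS result can be read as equal analgesia. It should be corrected before unblinding.

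**What to change.** - **Morphine, 0 to 24 h.** Report the Hodges-Lehmann shift, or the ratio of consumption, with its confidence bound in place of a Mann-Whitney p-value. Present it beside the primary VAS result, whose window it matches. The 24 h reading is already collected.
- **Non-inferiority label.** Keep it for morphine and for VAS at 48 h, 72 h and 7 days only where a margin on the right scale, with its rationale and the bound to be compared with it, is fixed before unblinding. If the SAP already holds such margins, cite them and align the test wording. Otherwise drop the label and report each difference with a 95% CI.
- **No gate on the primary claim.** Making the VAS conclusion conditional on morphine is not recommended. With truly equal use, a ratio margin of 1.2 would be met in only about 23 to 52% of trials under the assumptions above, and the trial was sized for VAS alone.

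The cost is a change of analysis wording, with no new data or patients. The drawback is that the morphine and later VAS results may no longer be described as non-inferior, and any tight morphine margin that is kept will have low power.
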